### Inclusion and Exclusion Criteria

Eligibility criteria is the presence of manic polarity symptoms during a moderate or severe depressive episode of BD I, BD II or MDD. We set the Montgomery–Åsberg Depression Rating Scale (MADRS) (48) with a score between 20 and 34 points for the definition of moderate major depressive episode and above 34 points for severe major depressive episode. The definition of major depressive episode with mixed features will be performed using the Young Mania Rating Scale (YMRS) (49) with ≥1 point on three or more items according to criteria used in the International Mood Disorders Collaborative Project (12) and consist with other definitions of depression with mixed features (50–53). Patients will be included in any appropriate pharmacological regimen (first or second line) according to the Canadian Network for Mood and Anxiety Treatments (CANMAT) guidelines to treat a major depressive episode of MDD or BD (I or II) (54, 55) and still have mixed depressive symptoms, so that TBS will be applied as an add-on treatment. We will not make adjustments to patient treatments, we will only enroll patients that are already on a stable psychopharmacological regimen (at least one month) of first or second line according to CANMAT but with no response/remission or partial response (still meeting inclusion criteria). The pharmacological regimen should be maintained on the same schedule and dosage from the beginning to the end of the study and patients will not be in a psychotherapy regimen. Drugs such as benzodiazepines will only be allowed at low doses (less than 3 mg per day of lorazepam or equivalent). Exclusion criteria will be: concomitant diagnosis of other neuropsychiatric disorders such as: schizophrenia, dementias, mental retardation, organic mental disorder, or epilepsy; psychotic depression; acute suicide ideation (assessed by interview and clinical evaluation); suspected or confirmed pregnancy; women in breastfeeding; severe or unstable clinical disease; specific contraindications to TBS (previous epileptic seizures; change in electroencephalogram at some point in life; previous stroke; previous severe TBI (with neurosurgery); metallic object on head (except mouth) as projectile piece, surgical clip, welding fragments; any implanted device (cardiac pacemaker, intravenous catheter). Personality, anxiety, and substance use disorders will be allowed as comorbidity provided the primary diagnosis is BD or MDD.

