Clinical assessments will be conducted weekly until the end of week 3 and thereafter a final assessment will be conducted at the end of week 6. Adverse events will be evaluated every day during the first week and then once a week until the end of the week 6. The neuropsychological assessment battery will be applied before the patient is stimulated and at the end of the week 6 of intervention (**Table 2**).

**Table 2 T2:** Measurement outcomes over time.

Scales	Baseline	End of week 1	End of week 2	End of week 3	End of week 6
SCID I/P modified	X				
MADRS	X	X	X	X	X
YMRS	X	X	X	X	X
*WHOQOL-bref*	X	X	X	X	X
BIS-11	X	X	X	X	X
CGI-S	X	X	X	X	X
GAF	X	X	X	X	X
HAM-A	X	X	X	X	X
BRIAN	X	X	X	X	X
Morningness–Eveningness Questionnaire	X				
TMS' Typical side Effects Scale	X	X	X	X	X
UKU-SERS	X	X	X	X	X
Neuropsychological Assessment	X				X

SCID, Structured Clinical Interview; MADRS, Montgomery–Åsberg Depression Scale; YMRS, Young Mania Rating Scale; WHOQOL, World Health Organization questionnaire; BIS-11, Barratt Impulsivity Scale; GAF, Global Assessment of Functioning; HAM-A, Hamilton Anxiety Scale; BRIAN, Biological Rhythm Interview of Assessment in Neuropsychiatry; TMS, transcranial magnetic stimulation; UKU-SERS, Udvalg for Kliniske Undersøgelser Side Effect Rating Scale; CGI-S, Clinical global impression - Severity.

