Primary outcome will be change in MADRS from baseline to week 3. Secondary outcomes will be: change in YMRS at the end of week 3 and 6 of treatment; response rates (50% or more of reduction in MADRS at the end of weeks 3 and 6 of treatment); remission rates (MADRS <11 (56) at the end of weeks 3 and 6 of treatment); change in anxious symptoms assessed by Hamilton Anxiety Scale (HAM-A) (57) at the end of weeks 3 and 6 of treatment; change in overall clinical impression assessed by Global Clinical Impression of Severity (GCI-S) (58) and Global Assessment of Functioning (GAF) (59) at the end of weeks 3 and 6 of treatment; change of functionality assessed by abbreviated version of the World Health Organization questionnaire (WHOQOL) (60) at the end of weeks 3 and 6 of treatment; change of biological rhythms assessed by the Biological Rhythm Interview of Assessment in Neuropsychiatry (BRIAN) (61) at the end of weeks 3 and 6 of treatment; change of impulsivity assessed by Barratt Impulsivity Scale (BIS-11) (62) at the end of weeks 3 and 6 of treatment; association between the chronotype assessed by Morningness–Eveningness Questionnaire (63) and the severity of mixed depression assessed by MADRS; and change in neuropsychological battery parameters before and at the end of the intervention (6 weeks).

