### Statistical Analysis

Statistical analyses will be performed using Stata^®^ (67) and the Statistical Package for the Social Sciences—SPSS^®^ (68). The overall significance level for this study will be 0.05 using two-tailed tests. The study results will be analyzed for two patient populations: the intention-to-treat (ITT(and the per-protocol (PP) analysis set. The ITT set will include all subjects who met the study eligibility criteria and received at least one week active/sham TBS treatment. The PP population thus will include all subjects from the ITT set who receive the protocol-specified treatment and complete the 6-week treatment regimen or withdrew before completion per the study protocol. Comparisons of baseline demographic and clinical characteristics and safety assessments will be performed on the ITT analysis set. The primary efficacy analysis will be performed using the PP analysis set.

Comparisons of baseline demographic and clinical characteristics between the study groups will be performed to ensure that the groups are balanced at baseline and that the randomization is successful. For comparison of means (continuous variables), the two-sample t-test or a nonparametric equivalent will be used. For comparison of proportions (categorical variables), the chi-square test or Fisher's exact test will be used, as appropriate. The change in MADRS total score from baseline to week 3 (primary endpoint) will be compared between the treatment groups using a linear mixed model (69) with a continuous dependent variable (MADRS score) to measure the primary outcome. For primary outcome subject will be the random effect and the fixed factors will be intervention (sham × active). Secondary outcomes will also follow the same pattern and the scales' scores will be the random effect and the fixed factors will be intervention (sham × active). Since patients will be taking different medications and dosages, the defined daily dose (DDD) will be used in the statistical analysis. This enables the inclusion of several medications and doses in the model, as medication groups (e.g., antidepressants, anticonvulsants, etc.).

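### The primary MADRS model names subject as the random effect; read plainly this is a random intercept, and the week-3 contrast may then not hold its two-sided 5% level

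*Protocol article*

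**What the plan says.** - **Endpoint** (Measurement of Variables and Outcomes): "Primary outcome will be change in MADRS from baseline to week 3".
- **Model** (Statistical Analysis): groups are compared "using a linear mixed model (69) with a continuous dependent variable (MADRS score") as the response. The section continues "For primary outcome subject will be the random effect" and "the fixed factors will be intervention (sham × active"). It mentions no random slope, residual covariance, visit term or intervention-by-visit term, and does not say which visits enter.
- **Level** (Statistical Analysis): "The overall significance level for this study will be 0.05 using two-tailed tests".
- **Ratings** (Inclusion and Exclusion Criteria, with Table 2): "Clinical assessments will be conducted weekly until the end of week 3", then once more at week 6. MADRS is therefore rated at baseline and weeks 1, 2, 3 and 6.
- **Entry** (Inclusion and Exclusion Criteria): a moderate episode is defined "with a score between 20 and 34 points for the definition of moderate major depressive episode" and a severe one as above 34. Every patient thus enters with a MADRS of at least 20.

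**The concern.** A mixed model whose only covariance term is a subject effect, with independent residuals of constant variance, is a random-intercept model. It assumes one variance at every visit and one correlation for every pair of visits.

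Two features of the trial make that unlikely. The entry floor narrows the baseline spread, whereas later scores may run from remission (MADRS below 11) to non-response. And the ratings lie one to six weeks apart, so neighbouring ratings would ordinarily correlate more strongly than distant ones.

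The primary test concerns one particular change, baseline to week 3. The random-intercept model does not estimate the variance of that change directly; it pools over all pairs of visits in the model. If the pooled value is smaller than the true one, the confidence interval is too narrow and a null trial is declared positive more often than the stated 5%. If it is larger, power is lost.

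**Working it through.** **Model examined.** As listed, with intervention as the only fixed factor, the model has no week-3 contrast. Its intervention test compares subject means and keeps its level (simulated 4.5-5.5%), but it does not test change to week 3. The check therefore adds visit and intervention-by-visit terms and asks what a random intercept does to the week-3 contrast.

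**Inputs from the protocol article.** 82 evaluable patients with 1:1 allocation, so n = 41 per arm; two-sided 5%; visits at weeks 0, 1, 2, 3 and 6.

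**Assumed inputs.** MADRS standard deviations and correlations are not given, so they are varied below. Data are taken as complete.

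**Formulas.**
- Model SE² = (2/n) × mean of Var(Yi − Yj) over all pairs of modelled visits
- True SE² = (2/n) × Var(Y3 − Y0)
- R = model SE / true SE
- Actual level = 2 × [1 − Φ(1.96 × R)]

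The factor 2/n cancels in R.

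**Example 1: SD 8 at every visit, correlation 0.8 per week apart.** Var(Yi − Yj) = 2 × 64 × (1 − 0.8^gap).
- Gaps of 1, 2 and 3 weeks give 25.6, 46.1 and 62.5. The true value is 62.5.
- Weeks 0-3: mean = (3 × 25.6 + 2 × 46.1 + 62.5)/6 = 38.6. R = √(38.6/62.5) = 0.786; level 12.4%. Two sets of 8,000 simulated trials gave 12.1% and 12.8%.
- All five visits: four more pairs, with gaps of 3, 4, 5 and 6 weeks (62.5, 75.6, 86.1, 94.4). Mean = 55.0; R = √(55.0/62.5) = 0.938; level 6.6% (simulated 6.6%).

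**Example 2: constant correlation 0.5, SDs 6, 7, 8, 9 at weeks 0-3 and 10 at week 6.** Var(Yi − Yj) = a² + b² − ab, where a and b are the two SDs. The true value for baseline to week 3 is 36 + 81 − 54 = 63.
- Weeks 0-3: (43 + 52 + 63 + 57 + 67 + 73)/6 = 59.2; R = 0.969; level 5.8%.
- All five visits: (355 + 76 + 79 + 84 + 91)/10 = 68.5; R = 1.043; level 4.1%, slightly conservative.

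**Example 3: correlation 0.8 per week, SDs 5, 7, 8.5, 9.5 and 10.5 at week 6.** True value 25 + 90.25 − 2 × 5 × 9.5 × 0.512 = 66.6. R = 0.776 and level 12.8% for weeks 0-3; R = 1.00 and level 5.0% with all five visits.

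**Range.** SD constant at 8, or rising from 6 to 9, 5 to 10 or 4 to 11 between baseline and week 3. Correlation constant at 0.3-0.7, or decaying at 0.5-0.9 per week. The end points shift a little with the SDs chosen for the other visits.

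| Visits in the model | Constant correlation | Decaying correlation |
|---|---|---|
| 0 and 3 | 5.0% | 5.0% |
| 0-3 | 5.0% with equal SDs; about 5.4-10.2% with unequal SDs | about 9.2-17.2% (SE 14-30% too small) |
| 0-3 and 6 | about 3.9-8.3% | about 4.9-9.8% |

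With two visits there is one pair, so R = 1 whatever the variances.

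**Under an unstructured covariance.** With complete data the week-3 contrast reduces to a t-test on the change score, which holds 5%. Simulation using the change's own variance gave 4.5-5.3%.

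**The case against.** **The text does not fix the residual covariance.** A subject random effect implies equal variances and correlations only if residuals are independent with constant variance. Residual structure and degrees-of-freedom method are details an article commonly leaves to a fuller document. This stands: a reader might infer that the plan forces the restrictive structure, and it does not. What remains is that the article does state the random part of its primary model, and the plain reading of that statement is a random intercept.

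**The week-3 standard error need not be wrong.** A reader might infer that it is always too small and that the error rate doubles. The level is exact with two visits and near 5%, or conservative, in many five-visit cases. Doubling needs weeks 0-3 only, independent residuals and, in most of the cases tried, correlation that decays with time. The article does not say which visits enter. Nor do short gaps dominate the full schedule: the ten gaps are 1, 1, 1, 2, 2, 3, 3, 4, 5 and 6 weeks, mean 2.8, against 3 for the primary contrast. For weeks 0-3 the mean gap is 10/6 = 1.7. This objection also stands.

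**The entry floor contributes less than assumed correlation decay.** With decay of 0.8 per week over weeks 0-3, moving from equal SDs to rising ones (Examples 1 and 3) raises the level only from 12.4% to 12.8%. A gentler assumption gives less inflation: at constant SD, with 40% of variance stable, 40% decaying at 0.8 and 20% rating error, R is 0.90 and the level about 8%. So equal variances and correlations are unlikely, not impossible.

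**The missing visit terms are the clearer defect.** Agreed, but adding them alone would leave the covariance question open.

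**Conclusion.** The concern holds in limited form. Read plainly, the stated primary model is a random intercept, and the standard error of its week-3 contrast then rests on an assumption that the entry floor and the uneven visit spacing make unlikely. The consequence runs from none (two visits), through about 4-10% (five visits), to about 5-17% (weeks 0-3), against a stated 5%.

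These figures rest on assumed SDs and correlations, complete data, independent residuals, and visit and intervention-by-visit terms that the article does not list. The protocol expects 10% dropout; its effect was not sized. The documents do not support saying that the trial's error rate is doubled. They support saying that its level is not secured by the model as described, and that a better model costs almost nothing.

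**What to change.** In Statistical Analysis, replace the subject random effect by a repeated-measures model over the scheduled MADRS visits, naming those visits. Include visit and intervention-by-visit terms, an unstructured within-subject covariance, and Satterthwaite or Kenward-Roger degrees of freedom. Take the intervention contrast for change from baseline to week 3 as the primary estimate. State the fallback if the fit does not converge: heterogeneous Toeplitz, or robust standard errors. Use the same structure for the continuous secondary scales.

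The cost is a short change of wording and some extra covariance parameters: 5 × 6/2 = 15 with five visits, against 2 for a random intercept with independent residuals. About 82 patients can support that. No further data or patients are needed.

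### The secondary-outcome model names the scale scores as the random effect; taken literally it cannot estimate a treatment effect, and its only stated fixed factor does not give the week 3 and week 6 contrasts

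*Protocol article*

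**What the plan says.** The Statistical Analysis section of the protocol article describes the primary analysis as a "linear mixed model (69) with a continuous dependent variable (MADRS score) to measure the primary outcome". It then specifies the terms: "For primary outcome subject will be the random effect and the fixed factors will be intervention (sham × active"). The next sentence deals with everything else: "Secondary outcomes will also follow the same pattern and the scales' scores will be the random effect", with intervention again given as the fixed factor. No secondary outcome is excepted.

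The section Measurement of Variables and Outcomes lists what that sentence has to cover. Most items are changes in continuous scales at the end of weeks 3 and 6; the neuropsychological battery is compared before treatment and at week 6. The list also contains two binary outcomes, "response rates (50% or more of reduction in MADRS at the end of weeks 3 and 6 of treatment") and "remission rates (MADRS <11 (56) at the end of weeks 3 and 6 of treatment"), and one item that does not compare the arms: "association between the chronotype assessed by Morningness–Eveningness Questionnaire (63) and the severity of mixed depression assessed by MADRS".

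One sentence in Statistical Analysis names a method for proportions: "For comparison of proportions (categorical variables), the chi-square test or Fisher's exact test will be used, as appropriate". It stands in the paragraph that opens with baseline comparability and comes before any efficacy endpoint is mentioned.

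**The concern.** A random effect represents the unit within which observations are correlated, here the patient. The score is what the model is meant to explain. Giving the score both roles is a wrong specification, not an abbreviated one. It also contradicts the instruction to use the same pattern as the primary outcome, so an analyst cannot obey both halves of the sentence.

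Nearly every secondary outcome depends on this sentence. An analyst will have to replace it with something workable, and the text does not fix what that is: which terms enter, how week 3 and week 6 are separated, and how the binary outcomes are handled. Those choices could then be made after the data are seen.

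**Working it through.** The plan gives no figure on this point, so there is none to reproduce. The check has three parts.

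**1. The sentence taken literally.**

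For patient i in arm g, with the score as grouping factor, the model is

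y_i = b0 + b1·g_i + u(y_i) + e_i,

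where u(y_i) is shared by all patients with the same score. Two patients from opposite arms with the same score share the same u, and their difference in y is exactly zero. Letting u take up the score fits the data perfectly, with b1 = 0 and no residual.

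Inputs to the simulation:
- 41 per arm, from the 82 participants in Sample Size Calculation.
- SD 8 points: an assumption, since the article gives none.
- Standardised difference that gives 90% power at two-sided 5%: (1.960 + 1.282) × √(2/41) = 0.716.
- True effect: -0.716 × 8 = -5.73 points.
- Scores rounded to whole points, one per patient, 100 runs.

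| Model | Mean treatment effect | Median residual variance |
|---|---|---|
| Ordinary regression on intervention | -5.50 | not recorded |
| Score as random effect, intervention fixed | -9 × 10⁻¹⁰ | 7 × 10⁻⁹ |

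The random effect absorbs the outcome. The SD only sets the scale; the collapse follows from the algebra above.

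**2. The sentence repaired, with only the stated fixed factor.**

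Let the score be the dependent variable and subject the random effect, with intervention alone as fixed factor. With complete data, the intervention coefficient is then the difference between arms in the patients' mean score over the visits entered. Table 2 has five assessments for most scales (baseline, weeks 1, 2, 3 and 6). Let δ be the effect at week 6 and take the baseline difference as zero. The time courses are assumptions:

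| Assumed course | Baseline included | Post-baseline only |
|---|---|---|
| Full effect from week 1 | (0+1+1+1+1)/5 = 0.80 δ | 4/4 = 1.00 δ |
| Linear rise to week 3, then held | (0+1/3+2/3+1+1)/5 = 0.60 δ | 3/4 = 0.75 δ |
| Two assessments (neuropsychological battery) | (0+1)/2 = 0.50 δ | 1.00 δ |

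Whatever the course, the result is one averaged number. It cannot give separate changes at weeks 3 and 6, which are the outcomes named.

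**3. Outcome types set against the stated pattern.**

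- Response and remission are yes/no at a visit; the pattern is a linear model for a continuous score.
- The chronotype item relates a questionnaire given only at baseline (Table 2) to MADRS. A model whose stated fixed factor is intervention has no term for it.

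**The case against.** The strongest reply is that this is a slip. The author probably meant that the scores are the dependent variable, and the same pattern would bring subject back as random effect. That is likely, but it is still the current text, and parts 2 and 3 of the check remain after the slip is corrected.

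A second reply is that visit terms are detail for a fuller document, that the abstract speaks of change over time and across groups, and that medication dose terms are also to enter, so the listed factor is not the whole model. This has some weight. But the abstract's phrase concerns the primary outcome, dose terms do not separate visits, and the article does state what the fixed factors will be. Separate fits to change scores at week 3 and at week 6 would need only intervention. They would, however, have one value per patient, which leaves a subject random effect nothing to estimate apart from the residual.

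A third reply is that the sentence on chi-square and Fisher tests covers response and remission, because these are proportions and the same-pattern sentence speaks of scale scores. This reading is possible. A reader might infer that the two outcomes have no valid analysis, but the article does not support that. The fault is that the method is not clearly assigned to them.

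A reader might also infer that repeated scores will be treated as independent, giving standard errors that are too small and an inflated false-positive rate. Nothing in the article specifies such a model. The literal wording collapses to a null estimate, and the repaired wording with subject as random effect allows for the correlation.

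**Conclusion.** The concern holds as an error in the stated rule for secondary outcomes. Naming the scale scores as the random effect is wrong and contradicts the sentence before it; fitted literally, the model estimates no treatment effect (about 0 against a true -5.73 points in the simulation, under the assumed SD of 8). Once that is corrected, intervention as the only stated fixed factor gives a visit-averaged difference: 0.60 to 0.80 of the week 6 effect for the five-visit scales and 0.50 for the two-visit battery if baseline scores are in the outcome, under the time courses assumed above. The week 3 and week 6 changes are not obtained. For response and remission the method is ambiguous.

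The weight is moderate. Only secondary outcomes are involved, the primary model is not touched by this sentence, and a literal fit would fail visibly rather than mislead. The wording error is certain. How far the other two gaps matter depends on how an analyst would fill them.

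**What to change.** Replace the sentence on secondary outcomes with the following content:

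- **Continuous scales:** the scale score is the dependent variable and subject the random effect. Fixed effects are intervention, visit, intervention-by-visit and the baseline value of that scale. Report the intervention contrasts at weeks 3 and 6; outcomes assessed only before treatment and at week 6 need only the week 6 contrast.
- **Response and remission:** name a binary-outcome method at weeks 3 and 6, for example a logistic model adjusted for baseline MADRS, or a risk difference with 95% CI. State whether the chi-square/Fisher sentence applies to baseline comparisons only.
- **Chronotype and MADRS:** take this out of the treatment-comparison model, describe it as a separate association analysis, and say which MADRS assessment is meant.

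The cost is wording only, with no change to visits, measurements or sample size. The article's Conclusion says recruitment was not complete at submission; the correction should be dated before unblinding.
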